### **8.6 Secondary outcomes**

Secondary Endpoint including:

- 1) The proportion of lupus low disease activity state (LLDAS) at week 96.
- 2) Short form-36 (SF-36) score of before and after treatment in two groups.
- 3) The proportion of adverse events of two groups in the follow-ups.
- 4) Changes in SLEDAI-2000 score.
- 5) Changes in prednisone dose.

In descriptive statistics, data were expressed in the form of frequency (percentages) for categorical variables (proportion of LLDAS, proportion of adverse events (AEs)), medians (interquartile) or means  $\pm$  standard deviations (SD) for continuous variables (SF-36 score variation, SLEDAI-2000 score variation and prednisone dose).

In addition, t-tests were used to compare between-group differences in continuous variables after exploring the normality of data distribution using the Shapiro-Wilk test. Mann-Whitney U tests were used to compare continuous variables with a skewed distribution. Pearson Chi-square or Fisher's exact tests were used to compare between-group differences in categorical variables. All tests were performed two-sided at the significance level of 0.05.

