## **7. Research interventions**

### **7.1 Research interventions**

#### **7.1.1 Description of Intervention**

Control group received treatment with HCQ (5mg/kg/day) and prednisone (0.5mg/kg/day); while MMF group received treatment with HCQ (5mg/kg/day) and prednisone (0.5mg/kg/day) plus MMF 500mg twice daily. Hydroxychloroquine is taken after meals and the manufacturer is Shanghai Pharmaceutical Co., Ltd, and the dosage form is tablets (100mg per tablet). The daily dose of mycophenolate mofetil is 500 mg twice daily, and the manufacturer is Hangzhou Zhongmei Huadong Pharmaceutical Co., Ltd., and the dosage form is capsule (250 mg per capsule).

Prednisone dose was tapered as follows: the initial dose was maintained for four weeks and then tapered 5mg every two weeks. When the dose reduced to 20 mg/day, it was tapered 5mg every month and then gradually to 0.1-0.2mg/kg/day. The taper of prednisone doses was determined by the physicians according to the assessment of the patients. Participants who met the criteria of severe flare were considered as having ended the trial and were treated with

increased doses of prednisone (more than 0.5mg/kg/day), immunosuppressive therapy or hospitalized for treatment according to the patients' condition and the physician's assessment.

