## 8. Study Intervention Discontinuation and Study Subject

### Discontinuation/Withdrawal

#### 8.1 Research Intervention Discontinuation

- 1) Patients who met the criteria of severe flare were considered as having ended the trial. Patients with severe flare were not eligible for the current treatment and need to be further evaluated by assessors, it may be necessary for them to discontinue study intervention, the patient will remain in the study to be evaluated for the remainder of the assessment visits.
- 2) Patients who met the criteria of severe flare were treated with increased doses of prednisone (more than 0.5mg/kg/day), immunosuppressive therapy or hospitalized for treatment according to the patients' condition and the physician's assessment.
- 3) Patients with mild-to-moderate flares continued to be followed up till the end of Week 96, and all flare episodes were recorded.
- 4) Patients with mild-to-moderate flares could increase the dose of prednisone (less than 0.5mg/kg/day) or nonsteroidal anti-inflammatory drugs.
- 5) For fever, rash, and arthritis, the dose of prednisone could be used at an initial dose of less than 0.5mg/kg/day, and following the assessment of symptoms, the dose could be increased to more than 0.5mg/kg/day if needed.
- 6) Any sign of kidney involvement (glomerular hematuria and/or cellular casts, proteinuria >0.5g/24hours (or spot urine protein-to-creatinine ratio (UPCR) >500mg/g), unexplained decrease in glomerular filtration rate (GFR)), renal biopsy was suggested to confirm the diagnose of LN.
- 7) The treatment of LN was provided according to the European Renal Association-European Dialysis and Transplant Association (ERA-EDTA) guideline.
- 8) The treatment of other organ involvement was provided following the 2019 European League Against Rheumatism (EULAR) recommendation.
- 9) Other situations:
  - a) Liver and kidney dysfunction (Alanine aminotransferase (ALT)/ aspartate aminotransferase (AST) > 2 times upper normal limits; creatinine clearance rate < 60ml/min),
  - b) Cancer,
  - c) Recent infection or hematologic diseases not caused by SLE,
  - d) Pregnancy or planned to be pregnant,
  - e) Patients not willing to join the study.

Other situations including liver or kidney dysfunction, cancer, recent infections or hematologic diseases not caused by SLE, pregnancy or planning to be pregnant, patient will also remain in the study to be evaluated for the remainder of the assessment visits.

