### **9.3.2 Serious Adverse Event (SAE) Definition**

Adverse medical events at any dose as defined by ICH-GCP:

Cause death;

Life threatening;

Requiring hospitalization or prolonged hospitalization;

Resulting in permanent or severe disability/incapacity;

Congenital malformations/birth defects.

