#### **9.3.4 Timing, frequency, follow-up, and regression of adverse event assessments**

The nature of the adverse event was determined by combining the definitions of AE and SAE from the ICH-GCP and GCP. All AEs including local and systemic reactions should be collected using a case report form (CRF) that collects information including description of the event, time of occurrence, physician's assessment of severity, relationship to the investigational product, and time to resolution/stabilization of the event. All AEs should be given adequate resolution. At each study follow-up visit, the investigator will ask about AEs/SAEs that have occurred since the

last follow-up visit, and the AE/SAE will be followed until resolved or stabilized.

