## 4. Study design

In this study, we randomly assigned patients (1:1) to Control group and MMF group. Control group received treatment with HCQ (5mg/kg/day) and prednisone (0.5mg/kg/day); while MMF group received treatment with HCQ (5mg/kg/day) and prednisone (0.5mg/kg/day) plus MMF 500mg twice daily. The dose of MMF stayed the same unless a contrary or severe adverse event occurred.

Prednisone dose was tapered as follows:

Initial dose (0.5mg/kg/day) maintained for four weeks

[figure not shown]

tapered 5mg every two weeks till to 20 mg/day

↓

tapered 5mg every month

↓

gradually to 0.1-0.2mg/kg/day

The taper of prednisone doses was determined by the physicians according to the assessment of patients.

Notes:

- 1) Patients with severe flare were not involved in subsequent treatment plan, but they were still being followed up consistently until the end of the entire process.
- 2) Patients who met the criteria of severe flare were treated with increased doses of prednisone (more than 0.5mg/kg/day), immunosuppressive therapy or hospitalized for treatment according to the patients' condition and the physician's assessment.
- 3) Patients with mild to moderate flares continued to be followed up till the end of Week 96, and all flare episodes were recorded.
- 4) Patients with mild to moderate flares could increase the dose of prednisone (less than 0.5mg/kg/day) or nonsteroidal anti-inflammatory drugs.
- 5) For fever, rash, and arthritis, the dose of prednisone could be used at an initial dose of less than 0.5mg/kg/day, and following the assessment of symptoms, the dose could be increased to more than 0.5mg/kg/day if needed.
- 6) Any sign of kidney involvement (glomerular haematuria and/or cellular casts, proteinuria >0.5g/24hours (or spot urine protein-to-creatinine ratio (UPCR) >500mg/g), unexplained decrease in glomerular filtration rate (GFR)), renal biopsy was suggested to confirm the diagnose of LN. Results of renal biopsy were confirmed by a senior nephrologist ([name]). The treatment of LN was provided according to the European Renal Association-European Dialysis and Transplant Association (ERA-EDTA) guideline.
- 7) The treatment of other organ involvement was provided following the 2019 European League Against Rheumatism (EULAR) recommendation.

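### Adverse events are compared over all follow-up with no companion analysis that stops at severe-flare rescue; if control has more severe flares, any MMF excess is diluted

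*Combined protocol and SAP*

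**What the plan says.** - **Endpoint and test.** SAP 8.6 lists "The proportion of adverse events of two groups in the follow-ups" among the secondary outcomes and says "Pearson Chi-square or Fisher's exact tests were used to compare between-group differences in categorical variables", two-sided at 0.05. Table 4 gives totals and event types by arm with a P value.
- **Collection.** Protocol 9.3.4: "At each study follow-up visit, the investigator will ask about AEs/SAEs that have occurred since the" last visit. The schedules in protocol 7.6 and SAP 12 carry this to week 96. Onset time and relationship to the product go on the case report form.
- **After a severe flare.** SAP 4, note 2, has these patients "treated with increased doses of prednisone (more than 0.5mg/kg/day), immunosuppressive therapy or hospitalized for treatment". Under note 1 they leave the treatment plan, but "they were still being followed up consistently until the end of the entire process". Protocol 8.1 also says "the patient will remain in the study to be evaluated for the remainder of the assessment visits".
- **Conflicting text.** Protocol 7.1.1 says "Participants who met the criteria of severe flare were considered as having ended the trial". Protocol 7.1.2 and the opening sentence of 8.1 say the same.
- **What rescue may contain.** The severe-flare definition in SAP 3.1 names added cyclophosphamide, azathioprine, methotrexate and MMF.
- **Analysis sets.** SAP 7 defines only an ITT and a per-protocol set. No on-treatment window, person-time rate or split at rescue is given.

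**The concern.** SAP 2 sets out to explore the efficacy and safety of MMF. A reader will take Table 4 as the answer on safety: what MMF adds to HCQ and prednisone. But a patient rescued for a severe flare is no longer on the assigned regimen, and events on rescue still count under the arm of randomisation. A control patient rescued with MMF could have an MMF-related event recorded as a control event.

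The protocol itself gives reason to expect toxicity from rescue. Section 9.3.1 names infection as the most common adverse event of both glucocorticoids and immunosuppressants. Section 2.2 cites an infection risk of 1.85 above 20 mg/day of prednisone, against 1.1 at 5 mg/day or less.

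If severe flares are more frequent in control, these events fall more on control and the arms look more alike than the assigned regimens are. The better MMF prevents severe flares, the stronger the dilution.

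A second gap is that the plan does not say whether a lupus flare, or a hospital stay for one, enters Table 4. The adverse-event definition in protocol 9.3.1 is the general one, and 9.3.2 makes an event serious if it is "Requiring hospitalization or prolonged hospitalization".

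**Working it through.** **Inputs from the documents.** Assumed flare rates of 30% (control) and 10% (MMF), for all flares (SAP 6); 65 patients per arm. The documents give no severe-flare rate by arm, no adverse-event rate and no event risk on rescue. Those are assumed below.

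**The plan's own figure.** Exact binomial enumeration of the two-sided unpooled Z test at 58 per group, 10% against 30%, gives power 0.8036, and actual alpha 0.0568 with both arms at 30%. Both match. 58 / 0.90 = 64.4, rounded up to 65. No figure is stated for the adverse-event comparison.

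**Where rescue would fall.** Expected flares are 65 × 0.30 = 19.5 in control and 65 × 0.10 = 6.5 on MMF, so 19.5 / 26 = 75% are in control. This carries over to rescue only if severe flares split as all flares do.

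**Formula, per arm.** Observed proportion = b + (1 − b) × s × q, where b is the proportion with an event on assigned treatment, s the severe-flare proportion, and q the chance of an event on rescue in a patient otherwise free of one.

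**Illustration A.** b = 25% control and 40% MMF (true excess 15 points, RR 1.60).

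| Severe flare, control / MMF | q | Control | MMF | Difference | RR |
|---|---|---|---|---|---|
| 10% / 3% | 0.30 | 27.25% | 40.54% | 13.3 points | 1.49 |
| 15% / 5% | 0.50 | 30.63% | 41.50% | 10.9 points | 1.36 |
| 20% / 7% | 0.50 | 32.50% | 42.10% | 9.6 points | 1.30 |

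Last row: 0.25 + 0.75 × 0.20 × 0.50 = 0.325; 0.40 + 0.60 × 0.07 × 0.50 = 0.421.

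**Illustration B.** b = 30% and 45%, half of planned flares severe (15% / 5%), q = 0.5. Control: 0.30 + 0.70 × 0.15 × 0.5 = 0.3525. MMF: 0.45 + 0.55 × 0.05 × 0.5 = 0.4638. The difference is 11.1 points, so 26% of the excess is lost. Power at 65 per arm falls from 0.42 to 0.25.

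**Wider grid.** Severe share of flares 25% to 100%, control b 20% to 40%, excess 10 to 20 points, q 0.25 to 0.75: the loss is 0.8 to 13.5 points. The excess vanishes or reverses in 2 of 108 scenarios. A 100% severe share is an upper bound.

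**Equal severe-flare rates** (b = 30% / 45%, q = 0.5). At 20% in both arms: 50.5% − 37.0% = 13.5 points, a loss of 1.5. At 10%: 47.75% − 33.5% = 14.25 points, a loss of 0.75, or about 0.8.

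**Check on the formula.** It adds rescue risk to a full period of base risk, although rescue time replaces assigned time. With a constant hazard, flare at mid-study and the last row of A: control 0.80 × 0.25 + 0.20 × (1 − √0.75 × 0.5) = 0.313; MMF 0.93 × 0.40 + 0.07 × (1 − √0.60 × 0.5) = 0.415. The loss is 4.9 points instead of 5.4. For the first row it is 1.3 instead of 1.7.

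**If counting stopped at severe flare.** Same assumptions as the last row: control 0.80 × 0.25 + 0.20 × (1 − √0.75) = 0.227; MMF 0.93 × 0.40 + 0.07 × (1 − √0.60) = 0.388. The difference is 16.1 points (RR 1.71), a little above the true 15, because control loses more time at risk.

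**The case against.** - **The all-follow-up comparison by arm is legitimate.** It is the treatment-policy contrast: what happens to patients started on each strategy, rescue included. This stands, and it should be kept. The gap is that it is the only comparison planned.
- **A cut at rescue has its own bias.** It is informative and shortens control exposure more; the last calculation shows it erring the other way. Rates per patient-year help fully only if the hazard is constant, and prednisone is highest early. This stands as a reason not to replace the main comparison.
- **Post-rescue events may not be counted at all.** The text treating severe-flare patients as having left the trial allows that reading. SAP 4 and the rest of protocol 8.1 make continued follow-up the likelier one, but the passages conflict. Either way a window must be stated.
- **Causality is collected.** Protocol 9.3.3.2 has a five-level relatedness scale. Protocol 10.3 lists individually the events leading to discontinuation and the treatment-related serious events, and permits reporting by association. That helps for rare serious events, but it is not a split at rescue, reporting by association is optional, and neither SAP 8.6 nor Table 4 uses it.
- **Double counting of flares.** A reader might infer that hospitalised flares are counted again as serious adverse events. The documents do not say so: flares have their own table, and Table 4 has no row for flares or serious events. What can be said is that the plan leaves it open.

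**Conclusion.** The point holds as a missing companion analysis. As planned, severe-flare patients who stay in follow-up contribute post-rescue events to their randomised arm, and nothing separates them. If severe flares are more frequent in control, any MMF excess is diluted. That direction rests on the trial's own hypothesis, which is stated for all flares; milder flares are managed with a smaller prednisone increase or NSAIDs (SAP 4, note 4), not with this rescue.

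The size cannot be fixed from the documents. Under the assumptions of illustration A, 15 points show as about 10 to 13; with similar severe-flare rates little is lost.

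A reader might go further and infer that the plan hides MMF's harm, or that rescue toxicity is known to fall mainly on control. Neither is supported. In nearly all scenarios tried most or some of the excess remains, and no severe-flare rate by arm is given.

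**What to change.** 1. Keep the all-follow-up comparison in SAP 8.6 and Table 4, labelled as the treatment-policy contrast.
2. Add a companion table of events with onset from first dose to first severe-flare rescue or stop of assigned treatment, whichever is earlier. Give patients with an event and events per patient-year, by arm. Show post-rescue events separately.
3. State that lupus flares and hospital stays for them appear in a separate row and are not part of the Total AEs row.
4. Reconcile protocol 7.1.1, 7.1.2 and the first sentence of 8.1 with the rest of 8.1 and SAP 4, because this decides which events are counted.

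The cost is SAP wording and one table. Event onset times (protocol 9.3.4), medication records (protocol 7.5 and 7.6) and the flare dates needed for the Kaplan-Meier analysis are already part of the plan. The downside is that the companion table is not a full-randomisation comparison and its cut is informative, so the two tables must be read together.

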### **9.3.3 Adverse event classification**

#### **9.3.3.1 Incident Severity**

Classified according to the Common Terminology Criteria for Adverse Events (CTCAE) version 5.0:

CTCAE provides a specific clinical description of the severity of each adverse event (Grade 1 to 5) based on the following basic guidelines.

Grade 1: Mild; asymptomatic or mild; seen clinically or diagnostically only; no treatment required

Grade 2: Moderate; requires lesser, local or non-invasive treatment; age-appropriate instrumental limitation of activities of daily living.

Grade 3: Severe or medically significant but not immediately life-threatening; results in hospitalization or prolonged hospitalization; disability; autonomic limitation of activities of daily living.

Grade 4: Life-threatening; requires urgent treatment.

Grade 5: Death related to AE.

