## **10.3 Security Analysis**

AEs are coded and calculated and may be expressed using severity, frequency, and association with the intervention. Adverse events leading to discontinuation of the research intervention and serious AEs resulting from treatment should be listed individually.

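### The only planned comparison of harm is the proportion with adverse events, in total and by type; no specified comparison uses the number, timing or grade of events, and the counting unit is undefined

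*Combined protocol and SAP*

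**What the plan says.** Secondary endpoint 3 is the proportion of AEs in the two groups during follow-up (SAP 3.2 and 8.6). SAP 8.6 summarises it as "frequency (percentages) for categorical variables (proportion of LLDAS, proportion of adverse events (AEs"). For the test it says "Pearson Chi-square or Fisher's exact tests were used to compare between-group differences in categorical variables", and then "All tests were performed two-sided at the significance level of 0.05".

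The Table 4 shell in SAP 15 has N (%) per arm and a P value column. Its rows are total AEs, infection and six infection sites or types, gastrointestinal events, bone fracture, osteonecrosis of the femoral head, and other events. It has no column for number of events, person-time, effect size or confidence interval, and no row by grade.

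Data collection is richer. Protocol 9.3.4 says "All AEs including local and systemic reactions should be collected using a case report form (CRF"), and the items include "time of occurrence, physician's assessment of severity, relationship to the investigational product" and the time to resolution. Protocol 9.3.3.1 sets the grading: "Classified according to the Common Terminology Criteria for Adverse Events (CTCAE) version 5.0", grades 1 to 5. Protocol 10.3 adds that AEs "may be expressed using severity, frequency, and association with the intervention". It also asks for individual listing of AEs that lead to discontinuation and of serious AEs resulting from treatment.

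**The concern.** SAP 2 states the aim as efficacy and safety, and protocol 9.3.1 names infection as the most common AE of both drug classes. Both arms start prednisone at 0.5 mg/kg/day and are followed to 96 weeks, so repeated mild events in both arms are plausible. If N counts patients, one upper respiratory infection and five in the same patient fill the same cell, and a grade 2 and a grade 4 pneumonia are not separated. If N counts events, a chi-square test treats repeat events in one patient as independent, and a percentage of patients has no clear meaning.

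What is at stake is how a non-significant P value in Table 4 will be read. With about 60 patients per arm, no interval and no rate, it could be taken as evidence that adding MMF does not increase harm.

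**Working it through.** **The plan's own figure.** The only power statement concerns flares (SAP 6): 58 per group, 10% against 30%, unpooled Z test. Exact binomial enumeration reproduces it: power 0.8036, and alpha 0.0568 evaluated at 30%. Dropout: 58/0.9 = 64.4, so 65. No power or sample size is stated for AEs.

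**What a test of proportions can detect.** With 65 per arm and two-sided 0.05, the chi-square test reaches 80% power for absolute differences of about 19 points (control 10%), 24 points (control 30% to 50%) or 16 points (control 80%). With 58 per arm these become 21, 25 to 26 and 17 points.

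**Ever/never against rates.** Every AE input here is an assumption, because the documents give no AE rate, effect size or dispersion. Inputs are control mean m over 96 weeks, rate ratio RR, dispersion k, n = 65 per arm and full follow-up.

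- Proportion with at least one event: 1 − (1 + k·m)^(−1/k); for Poisson counts, 1 − e^(−m). Power is exact for the Pearson test.
- Rate comparison: Wald test of log RR, with SE = √[(1/m + 1/(m·RR) + 2k)/n].

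Worked case with m = 1, k = 1, RR = 1.5:
- The proportions are 1 − 1/2 = 50% and 1 − 1/2.5 = 60%, and the ever/never power is 20%.
- SE = √[(1 + 0.667 + 2)/65] = 0.2375, and ln 1.5/SE = 0.4055/0.2375 = 1.71. Power is Φ(1.71 − 1.96) = 40%.

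| m | k | Control / MMF with ≥1 AE | Ever/never power | Rate power |
|---|---|---|---|---|
| 1 | 0.5 | 56% / 67% | 29% | 52% |
| 1 | 1 | 50% / 60% | 20% | 40% |
| 2 | 0.5 | 75% / 84% | 24% | 68% |
| 2 | 1 | 67% / 75% | 19% | 49% |
| 3 | 0.5 | 84% / 91% | 20% | 75% |
| 3 | 1 | 75% / 82% | 16% | 53% |

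All rows use RR = 1.5. The ranges are 16% to 29% against 40% to 75%.

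**Sensitivity.**
- RR = 2, same m and k: 33% to 66% against 85% to over 99%.
- RR = 2, Poisson counts, m = 0.5 to 2: ever/never power is 77% to 88%.
- RR = 1.5 with 20% of controls having an AE, Poisson to k = 1: 16% to 20% against 20% to 22%, so counts add almost nothing.
- RR = 1.5 with any control proportion from 10% to 90%: ever/never power stays below 50%, both for Poisson counts and for k = 1.

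**Precision of the added estimate.** For an observed rate ratio of 1.5, m = 1 and k = 1 give a 95% CI of 1.5 ÷ and × exp(1.96 × 0.2375), that is 0.94 to 2.39. With m = 3 and k = 0.5, SE = √[(0.333 + 0.222 + 1)/65] = 0.1547 and the interval is 1.11 to 2.03.

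**The case against.** A reader might infer that harm is tested only as any AE, yes or no, and that counts and grades are ignored. The documents do not support that. Table 4 has separate rows for infection, pneumonia, gastrointestinal events, fracture and osteonecrosis, each with a P value. Protocol 10.3 permits description by severity and frequency and requires individual listings of treatment-related serious AEs and AEs leading to discontinuation. What stands is narrower: each Table 4 row is still N (%), the provision in 10.3 is optional and has no method or table shell, and listings are not a comparison between arms.

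A reader might also infer that the yes/no measure saturates, so that a real excess will usually be missed. Neither follows from the documents, which give no AE rates. In the assumed cases 50% to 84% of controls have an AE, and at 50% the measure is not saturated, yet power is still only 20%. Much of the shortfall is therefore sample size. With Poisson counts and a true doubling, the test of proportions does well over much of the range.

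The practical objections have weight. Patients are asked about AEs at visits 24 weeks apart and only assessors are masked (protocol 6.5), so counts of mild events depend on recall and on unmasked reporting. A rate also needs a defined time at risk. Protocol 7.1.1 says severe flare ends the trial. Protocol 8.1 says that too, but keeps the patient in for the remaining visits, and SAP 4 continues follow-up. These points limit what a rate ratio can show. They do not defeat adding one beside the existing rows, and unequal follow-up would distort the crude proportion as well.

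**Conclusion.** The point holds as a gap in specification. The sole planned between-arm comparison of harm is a proportion, in total and by type, with no interval in the AE table. It does not use the number, timing or CTCAE grade of events that the CRF is meant to collect, and its counting unit is undefined.

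The size is conditional. If AEs are recurrent and overdispersed (control mean 1 to 3, dispersion 0.5 to 1) and the true rate ratio is 1.5, moving from ever/never to rates raises power from 16% to 29% up to 40% to 75%. If AEs are rare the gain is negligible, and no method makes 65 per arm adequate for modest excesses. The justified conclusion is that a non-significant P value in Table 4 should not be read as showing no difference in harm. It is not established that an excess would usually be missed.

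**What to change.** In SAP 8.6 and Table 4:

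1. Define N as patients with at least one event, and keep all present rows on that basis.
2. Add the number of events and the rate per 100 patient-years in each arm.
3. For all AEs and for infections, add a rate ratio with 95% CI from a negative-binomial model with log observed follow-up time as offset.
4. Add rows for patients with any grade 3 or higher AE and any grade 3 or higher infection.
5. State that these are read as estimates, and that a non-significant result is not proof of no difference.

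Before that, reconcile protocol 7.1.1, 7.1.2 and 8.1 with SAP 4 on follow-up after severe flare, so that observed time at risk has one definition.

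The cost is SAP wording, one model fitted to two outcomes and a few table rows; the event data are already specified for the CRF. There are two downsides. Rates can be driven by a few patients with many events, which the dispersion term and the retained patient-level rows help to show. Counts of mild events rest on recall over 24-week intervals and on reporting by unmasked patients, so the grade 3 or higher rows should be read alongside them.
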